**Methods:**

A cluster randomized trial, with the general practitioner office as the unit of randomization, has been designed to evaluate the effect of a referral intervention on the quality of health care delivered. Referral templates have been developed covering four diagnostic groups: dyspepsia, suspected colonic malignancy, chest pain, and chronic obstructive pulmonary disease. Of the 14 general practitioner offices primarily served by University Hospital of North Norway Harstad, seven were randomized to the intervention group. The primary outcome is a collated quality indicator score developed for each diagnostic group. Secondary outcomes include: quality of the referral, health process outcome such as waiting times, and adequacy of prioritization. In addition, information on patient satisfaction will be collected using self-report questionnaires. Outcome data will be collected on the individual level and analyzed by random effects linear regression.

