Many studies have been designed for improving the referral process from GPs to the hospital [16,17]. A recent Cochrane review on interventions to improve outpatient referrals from primary to secondary care concludes that surprisingly few interventions on the referral system have been rigorously evaluated. Many of the studies evaluated focused only on referral rates or referral quality. The review highlights the complexities of research in this area, especially as no single study managed to present findings on all aspects of the referral process (referral behavior, management of non-referred patients, secondary care management of patients, the flow of patients through the referral system, patient outcomes and satisfaction, and resource use). However, structured referral sheets and local education interventions have an impact on referral rates [18].

The primary objective of the present study is to evaluate whether the implementation of a referral template in the referral from general practice to hospital care can lead to a measurable increase in the quality of care delivered at the hospital. As secondary objectives, we will assess patient satisfaction and effective prioritization at secondary care.

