### Intervention

The referral templates have been developed based upon international literature [19-27] and in collaboration with local specialists in the appropriate medical field. The templates have also been through a process of clinical assessment from subspecialists in other northern Norwegian hospitals. In acknowledging the problems in earlier studies with the uptake of referral interventions [17,18] we have deliberately reduced the number of items in the referral templates, to ensure ease of uptake. Only information that the medical consultants thought imperative in the referral have been included as items in the templates. The study will implement referral guidelines for the following four diagnostic groups:

•
patients referred with dyspepsia;

•
patients referred with suspected colonic malignancy;

patients referred with chest pain;

•
patients referred with chronic obstructive pulmonary disease or suspected chronic obstructive pulmonary disease.

These diagnostic groups were chosen as they represent a substantial number of the referrals to a medical department (own data, 2008). They also represent a clear diagnostic challenge in primary care and are adept for simple referral guidelines.

The GPs at the intervention offices will use the referral template when initiating a new referral process for a patient. To ensure adequate uptake of intervention, the templates have been distributed as electronic templates as well as hard copies. The templates function as guidelines, but are not implemented as compulsory electronic checklists. The intervention referrals are sent to a separate electronic inbox at the hospital. The further evaluation and process of care has not been altered in the intervention group compared with the standard referral practice in the control group (Figure 3).

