As secondary outcomes, the quality of the referrals will be evaluated against the developed referral template, to determine if the intervention has led to improved referral quality. It is important to measure referral quality, as the premise in the study is that more information will lead to improved care. In addition, health process outcomes such as waiting time from referral to appointment, number of appointments before a diagnosis is reached, time before treatment is initiated, the application or not of appointment prioritization, and the outcome of any given referral (appointment, return information or referral rejected) will be collected and compared between the groups. Bennett *et al*. used the PPV of a referral as a measure of the appropriateness of the referral [31]. In adapting this concept from glue ear in otolaryngology to a medical department we have defined it as the proportion of the GP referrals that result in a histological diagnosis, diagnostic clarification or change in medical management. We will assess and compare the PPV of referrals in the study groups. Patient experiences will be compared between the intervention and control group. Finally, the possible outcome diagnoses have been grouped according to severity. We will correlate the continuous outcome variable ‘waiting time’ with the grouped severity, to see whether the prioritization in the intervention group is more aligned with disease severity.

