### Statistical methods

We will collect the following baseline characteristics:

• patient age (mean and confidence interval) and sex (number and percentage)

• practice list size (median and interquartile range, or mean and confidence interval if normally distributed)

• referral type - electronic or paper (number and percentage)

• referred by - GP or other doctor (number and percentage).

For the primary outcome (quality score), we will calculate adherence scores as described above and compare between treatment arms. We expect substantial variation in cluster size. Because of the small number of clusters, analysis based upon the cluster level was considered [41]. However, as there is no prior accurate estimate of variation between clusters, weighting for cluster size could not be achieved [41]. To offer increased precision and take into account between-cluster variation, random effects linear regression will be used [42] to generate estimates of intervention effect. It has been suggested that this can be used for studies with as few as 10 clusters [36]. The estimated effect and confidence intervals will be reported. A *P*-value <0.05 will be regarded as statistically significant. Intention to treat analysis will be employed.

The referrals will be scored using a simple scoring system related to the referral templates. Each unit of information specified in the referral template (for example, presence of weight loss specified) will provide one point in the scoring system, with no weighting applied. Scores will be compared between the groups as noted above.

For outcome severity, random effects linear regression will be used, with the severity group score as a categorical variable, and the relationship compared between the intervention and control group.

In the questionnaire, answers noted as ‘not applicable’ or no answer will be counted as missing data. The questionnaire will be scored according to a pre-set scoring system. Scores will be analyzed using the regression technique outlined above. The data will also be analyzed to determine if factors such as self-perceived health, age, gender, and education level have an impact on patient experience.

The trial will be reported according to the CONSORT standards for reporting cluster randomized trials [43].

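### The model for waiting time against severity pools four complaints without a diagnostic-group term, which can cost precision and leaves the arm comparison open to case-mix differences

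*Protocol article*

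**What the plan says.** Under Outcomes, the protocol article says that "the possible outcome diagnoses have been grouped according to severity". It continues: "We will correlate the continuous outcome variable ‘waiting time’ with the grouped severity". The stated aim is to learn whether waits in the intervention arm follow severity more closely than in the control arm. Under Statistical methods, the model is random effects linear regression, "with the severity group score as a categorical variable, and the relationship compared between the intervention and control group". This serves the secondary hypothesis of more appropriate prioritization listed under Objectives.

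The patients come from four complaints: "The study will implement referral guidelines for the following four diagnostic groups", namely dyspepsia, suspected colonic malignancy, chest pain and COPD. The abstract ties the primary score to these groups: "The primary outcome is a collated quality indicator score developed for each diagnostic group". Nothing similar is said of severity. Neither Outcomes nor Statistical methods names diagnostic group as a covariate, stratum or interaction in the severity model, and it is not among the listed baseline characteristics.

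**The concern.** A referral labelled "patients referred with suspected colonic malignancy" and one for dyspepsia may well differ in usual wait and in the likely severity of the final diagnosis, whatever the letter says. A regression over all patients then mixes two things: how waits and severity differ between complaints, and how well patients with the same complaint are ranked. Each template asks for information about its own complaint, so its most direct effect should be on the second.

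Three consequences are possible for the arm comparison:

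- Differences in usual wait between complaints inflate the residual variance.
- A within-complaint improvement may be diluted.
- If the arms have different mixes of complaints, the comparison can move with no change in ranking. There are only 14 clinics, substantial variation in cluster size is expected, and the Discussion names differing cohorts by arm as a risk.

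**Working it through.** The article gives no figure for this analysis, so there is none to reproduce. It also gives no waits, SD, complaint mix or severity distribution. Everything below except the 855 patients per arm (Sample size) is assumed. For simplicity, severity is a linear score 0, 1, 2 (the article uses categories), clustering is ignored and the test is two-sided at 5%.

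**Assumed inputs**, in the order dyspepsia, suspected malignancy, chest pain, COPD: equal mix; severity probabilities (0.70, 0.25, 0.05), (0.40, 0.30, 0.30), (0.50, 0.30, 0.20), (0.30, 0.50, 0.20); usual waits 90, 25, 40, 80 days; residual SD σ = 20 days; true improvement δ = 3.5 days per severity step.

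**Step 1: components.**
- Mean severity by complaint: 0.35, 0.90, 0.70, 0.90. Variances: 0.3275, 0.69, 0.61, 0.49.
- Severity variance: within complaints 0.5294, between 0.0505, total 0.5798. Between share λ = 0.0505/0.5798 = 0.087.
- Variance of usual waits between complaints: 729.7 (SD 27). Covariance with mean severity: −3.359.

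**Step 2: slope within one arm.** With no ranking at all within complaints, the pooled slope is −3.359/0.5798 = −5.8 days per step.

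**Step 3: arm contrast, same mix in both arms.** That −5.8 is in both arms and cancels. What remains depends on how usual wait is defined:
- If it is the wait at the lowest severity, the pooled contrast is δ = 3.5.
- If it is the complaint's mean wait, the pooled contrast is (1 − λ)δ = 0.913 × 3.5 = 3.2.

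**Step 4: precision.**
- Pooled residual variance = 400 + 729.7 − 3.359²/0.5798 = 1110. SE = √(2 × 1110/(855 × 0.5798)) = 2.12.
- With group means common to both arms: SE = √(2 × 400/(855 × 0.5798)) = 1.27.
- With group means also free by arm: SE = √(2 × 400/(855 × 0.5294)) = 1.33.

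Power = Φ(3.5/SE − 1.96), under the first definition in step 3:

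| Usual waits (days) | σ | Pooled | Common group means | Group means by arm |
|---|---|---|---|---|
| 90/25/40/80 | 20 | 38% | 79% | 75% |
| 90/25/40/80 | 30 | 28% | 45% | 42% |
| 90/25/40/80 | 40 | 21% | 28% | 26% |
| 90/25/40/80 | 60 | 13% | 15% | 14% |
| 65/45/50/60 | 20 | 73% | 79% | 75% |
| 65/45/50/60 | 30 | 43% | 45% | 42% |
| all equal | 20 | 79% | 79% | 75% |

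Simulation with common group means agrees closely: 38% v 77% in the first row and 21% v 29% in the third. Under the second definition, pooled power in the first row is Φ(3.2/2.12 − 1.96) = 33%.

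**Step 5: a second set of assumptions.** Mix 30/30/25/15%, waits 70/25/40/60, SD 30, 14 clinics of 122, within-complaint slope −3 (control) and −9 (intervention), usual wait taken as the complaint mean, group means free by arm. For λ = 0.017, 0.125 and 0.355:
- Pooled arm difference −5.9, −5.3, −3.9, against a true −6.
- Power 84%, 68%, 52% pooled; 94%, 83%, 77% adjusted.
- Rejection under the null, pooled: 3.8%, 5.0%, 4.7%.

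**Step 6: different mix by arm, no ranking in either arm.** In the step 1 setting, move ten points from dyspepsia to suspected malignancy in the intervention arm (15/35/25/25%). Covariance becomes −2.502 and severity variance 0.6034, so the slope is −4.15. The pooled contrast moves by −4.15 + 5.79 = +1.65 days, or 1.65/2.12 = 0.8 SE. The reverse shift gives −0.6. The same formula over all twelve ten-point shifts between two complaints gives −2.7 to +2.8. In simulation, the adjusted contrast stays near 0.

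**The case against.** The strongest reply is that the planned inference compares arms. A reader might infer that the analysis largely measures which complaint was referred, or that good alignment could be reported where none exists. That can describe a slope within one arm (step 2), but the article draws no conclusion from such a slope. With similar mixes the shared part cancels and the null rejection rate is near nominal. This part of the reply stands.

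The size also depends on chosen inputs. The 38% v 79% row needs complaint differences larger than the residual spread (SD 27 against 20), and the gain shrinks quickly as σ rises or waits converge. This stands too.

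Three further readings go beyond the text:
- That there is a single severity scale across complaints. It is the likely reading of Outcomes but is not stated. Grading within each complaint would weaken the point, though differing usual waits would still add noise.
- That the template cannot change which complaints are referred. The Background reports that "structured referral sheets and local education interventions have an impact on referral rates". This makes a mix difference more plausible, not less.
- That only ranking within a complaint counts as better prioritization. Objectives does not restrict the hypothesis in that way.

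Finally, a condensed article may leave covariates to a fuller plan. But it does state a specific model for this outcome, and the suggestion improves that model rather than asking for missing detail.

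**Conclusion.** The point holds in a limited form. As stated, the severity model pools four complaints with no diagnostic-group term. Where usual waits differ by complaint, this adds noise to the arm contrast, may attenuate it (2% to 36% in the step 5 scenarios, little or none in the first set) and exposes it to a difference in case mix. It does not by itself invalidate the test.

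Under assumed inputs, the benefit of adjustment runs from none (equal usual waits) to roughly a doubling of power (waits 90/25/40/80, SD 20). A ten-point mix shift could move the pooled contrast by up to about one SE or slightly more (2.8/2.12 = 1.3). No such imbalance is documented; the Discussion names the risk and describes recruitment meant to reduce it. This is a low-to-moderate priority improvement to a secondary analysis.

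**What to change.** In Statistical methods, add diagnostic group to the severity model so that each complaint has its own mean wait. State whether severity grades are comparable across complaints; if they are not, give each complaint its own severity terms. Define the arm contrast as the severity-by-arm term adjusted for diagnostic group, and report per-group results as description only. Fix in advance whether group means are common to both arms or free by arm.

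No new data are needed, since patients are recruited within one of the four groups. The cost is three parameters for the group means, three more if they are free by arm, and a few more for group-specific severity terms, against about 1,700 planned patients. If usual waits do not differ by complaint, common group means cost essentially nothing (SE 1.27 either way). Means free by arm raise the SE by about 5% (1.33/1.27).

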### Recruitment

New patients referred to the medical department within one of the four diagnostic groups described below will receive written information and a consent form together with their appointment letter. These will be sent out by a clinic nurse unaware of the status of the GP center sending the referral (intervention or control). Patients will be orally reminded at the appointment and may be given a new consent form. This process is illustrated in Figure 2.

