**Figure 3 F3:**
[figure not shown]
**Referral pathway.** Flow of referral and process of care in the intervention (blue arrows) and control group (red arrows).

In addition, questionnaires have been developed that assess patient experiences within the care framework, with one questionnaire designed for inpatients and one for outpatients. These questionnaires have been produced by combining questions from previously validated questionnaires regarding patient experiences in general and with transitional care. They include questions from a Norwegian patient experiences questionnaire [28]); two questions about health interaction from the Commonwealth Fund Survey 2010 [29]; the Care Transitions Measure 3 [30]; and demographic questions.

The questionnaires have been reviewed through an interview process with patients. This was done to ensure that the forms are acceptable to patients and to highlight possible issues that patients felt were missing from the questionnaires.

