In cluster randomized trials, post randomization bias has been identified as a concern [40]. This entails the recruitment of different cohorts in the intervention and control groups, as the patients are recruited after randomization of the clusters. We hope to reduce this by actively recruiting the patients (obtaining signed consent) in conjunction with the hospital appointment, both for the intervention and control groups.

The intervention is intentionally simple to ensure that an effect seen can be attributed to the intervention. However, an intervention at an interface in a complicated health care system can quickly affect the entire process, in ways we have not yet envisaged.

There is also a risk of performance bias as systematic differences in the care may not be due to the intervention, but rather because the doctors will be aware of the study protocol. By ensuring the mixing of cases in normal workloads and, as much as possible, blinding the doctors involved, we hope to minimize this bias. The fact that the care process is being studied may change the behavior of the doctors in general, akin to a Hawthorn effect. This will potentially attenuate the effects of the intervention, as the quality of care may improve for both intervention and control patients.

The authors also recognize that many referrals from primary to secondary care are not made only to identify major pathology. Referrals are also made to reassure the patient, reduce medico-legal risk, obtain a second opinion or for handing over of care [50]. The authors fully appreciate these as valid reasons for referral. We, therefore, do not aim to reduce the number of referrals, but rather assess the effect on hospital care of improved referrals.

This study aims to add to the knowledge regarding the effect of the referral on the patient pathway and quality of care. Simple diagnostic groups have been chosen. If the study can identify benefits from improving referrals in these areas, this may lead the way to further implementations of referral proforma, preferably electronically integrated into the standard software packages. This could improve the overall referral process to enable better care and effective prioritization based upon the need of the individual patients.

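### The protocol fears different patient cohorts in the two arms, but its stated arm comparison names no patient covariate, although age and sex are collected

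*Protocol article*

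**What the plan says.** In the protocol article, Statistical methods gives the primary analysis in one line: "random effects linear regression will be used [42] to generate estimates of intervention effect". The referral score is to be compared in the same way, and for the questionnaire "Scores will be analyzed using the regression technique outlined above". No patient covariate is named for any of these comparisons.

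Patient factors appear in two other places in that section. The list of baseline characteristics includes "patient age (mean and confidence interval) and sex (number and percentage". The questionnaire paragraph adds an analysis to "determine if factors such as self-perceived health, age, gender, and education level have an impact on patient experience". Education level is not in the baseline list. The likely source is the patient questionnaire, which (end of the Intervention section) contains "the Care Transitions Measure 3 [30]; and demographic questions".

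The Discussion names post-randomization bias as a concern: "This entails the recruitment of different cohorts in the intervention and control groups, as the patients are recruited after randomization of the clusters". The response is: "We hope to reduce this by actively recruiting the patients (obtaining signed consent) in conjunction with the hospital appointment". Recruitment adds a safeguard for the consent forms: "These will be sent out by a clinic nurse unaware of the status of the GP center sending the referral". Randomization was stratified by location, partly to even out sociodemographic background.

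**The concern.** Randomizing 14 clinics does not by itself balance patients who enter later. Three features of this trial add to the risk:

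- The referring GPs know their arm (Blinding), and one secondary hypothesis is that the template makes referrals more appropriate (Objectives). The mix of referred patients may therefore differ by arm before the hospital sees anyone.
- Every patient must give written consent (Ethics), so inclusion is selective in both arms.
- Two of the four rural clinics first randomized to the intervention refused and were replaced from the rural clinics first randomized to control (Figure 1 legend). Balance no longer rests wholly on the original allocation.

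The protocol sees this threat but carries no part of the answer into the arm model, although two relevant patient variables are at hand. If age or sex is related to an outcome and differs between arms, an unadjusted comparison counts that difference as an effect of the template. The primary quality score, the referral score, waiting time and patient experience are all open to this.

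**Working it through.** **Figures in the protocol.** It gives no covariate effect and no expected imbalance, so there is no figure on this point to reproduce. The inputs below that come from the protocol are the ICC range 0.001 to 0.08, 855 patients per arm, 14 clinics and the 10% difference. The stated design effects do follow from the stated cluster size of 150: 1 + 0.001 × 149 = 1.149 and 1 + 0.08 × 149 = 12.92.

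**Size of the bias (assumed inputs).** To first order, bias = slope × imbalance.

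| Assumed slope | Assumed imbalance | Bias (points) |
|---|---|---|
| 1 point per covariate SD | 0.1 SD | 0.1 |
| 2 points per SD | 0.3 SD | 0.6 |
| 4 points per SD | 0.5 SD | 2.0 |
| 0.2 to 0.4 points per year of age | 5 years | 1 to 2 |
| 5 points between education groups (questionnaire) | 10 percentage points | 0.5 |

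The age row lies at the upper end: 0.4 points per year is 16 points over 40 years. The protocol does not say whether its 10% is absolute or relative. Read as 10 points, a bias of 2 points is one fifth of it. Read as relative, the target in points is smaller and the share larger.

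**What adjustment removes.** A simulation of 150 trials used 14 clinics of 40 to 204 patients, ICC 0.03, an SD of about 20 and a true effect of zero. Age and an unmeasured severity factor each differed by 0.3 SD between arms, each with a slope of −3 points per SD.

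- Expected bias without age: −3 × 0.3 × 2 = −1.8. Simulated mean: −1.70.
- Expected bias with age in the model: −3 × 0.3 = −0.9. Simulated mean: −0.81.
- The SD of the estimates was 2.10 and 2.11, so the Monte Carlo error of each mean is about 2.10/√150 = 0.17. Both means agree with expectation.

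Adjustment removed the age part and left the severity part untouched.

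**Precision.** Let the covariates explain a share R² of the within-clinic variance, with m = 2 × 855/14 = 122 patients per clinic and R² = 0.10 (assumed):

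SE ratio = √{[ρ + (1−ρ)(1−R²)/m] / [ρ + (1−ρ)/m]}

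- ρ = 0.001: √(0.00837/0.00919) = 0.954, a fall of 4.6%.
- ρ = 0.02: √(0.02723/0.02803) = 0.986, a fall of 1.4%.
- ρ = 0.08: √(0.08679/0.08754) = 0.996, a fall of 0.4%.

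The case for adjustment therefore rests on bias, not on precision.

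**The case against.** The strongest reply is that the text is silent rather than wrong. A journal article may name the model and leave the covariates to an analysis plan, and nothing under Statistical methods rules out an adjusted analysis. That stands, and it limits the point: there is a gap between a named risk and the stated model, not a decision to exclude these factors.

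A reader might also infer that the protocol expects age, sex and education to matter. It does not say so. The sentence on these factors asks an open question about patient experience only, and nothing ties them to the quality score. Nor does the text say whether that further analysis includes the arm.

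A third inference would be that cohort differences pass unhindered into the estimates. The documents do not support that either. Clinics were stratified by location, the nurse sending consent forms does not know the arm, recruitment follows one procedure in both arms (Figure 2 legend), and tabulating age and sex would make an imbalance visible. The quality score is also a share of the criteria applicable to each patient, which may absorb some patient differences. These safeguards are partial. The nurse acts after the GP has chosen whom to refer, the stratum is only town or rural, and a table shows an imbalance without correcting it.

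Finally, age and sex are weak stand-ins for severity and case mix, the likelier route if the template changes who is referred. That is right, and the remedy must not be presented as more than it is.

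**Conclusion.** The point holds in a limited form. The protocol names different cohorts as a risk, meets it by design measures only, and states an arm comparison without the patient age and sex it collects. Differences in these may enter the effect estimates. Their size cannot be derived from the documents; 0.1 to 2 points rests wholly on assumed slopes and imbalances. Adjustment would remove the measured part only, and the gain in standard error is about 0.4% to 4.6% on an assumed R² of 10%. This is a worthwhile, inexpensive improvement to the analysis, not proof that the unadjusted result would mislead.

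**What to change.** Under Statistical methods:

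- Prespecify patient age and sex as fixed effects in the random effects model for the quality score and the continuous secondary outcomes, and report the unadjusted estimate beside the adjusted one. Both are needed: if the template changes whom GPs refer, the two answer somewhat different questions.
- In the questionnaire arm comparison, also include education level where the questionnaire supplies it.
- Keep self-perceived health out of that arm model. It may be reported after care, so the template may have affected it. It can stay in the further analysis of patient experience.
- State that adjustment deals only with these measured factors and leaves differences in severity or case mix.

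The cost is a few lines of wording. Age and sex are already collected and, being patient-level terms, take nothing from the limited information between 14 clinics. Education is probably known only for questionnaire responders and may be missing for some of them. Fixing the covariates now also prevents their being chosen after the results are seen.
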